### Data collection and management

Prospective data collection will be developed in consultation with experts from existing NAS programs and informed by the Minimum Dataset for NAS registry recommendations [56]. Anonymous LOS data will be collected from administrative data for NAS admissions at all sites pre-initiation and at each implementation phase for patients that are not consenting participants in the study. Standardized forms will be used to collect data, including LOS, for consenting participants at discharge and at 6 months follow-up (Table 1 ).

**Table 1 Tab1:** Data collection: rooming-in intervention economic evaluation, and short-term social, health, and developmental outcomes

All sites	Number of Mother &Infant Dyads	Months Collected	Data
**Baseline data** (Anonymous) Throughout all phases	160–240	6 – 27	LOS in NICU, pharmacological management, breastfeeding at discharge and apprehension rates
**During implementation-** (consenting participants at/before discharge)	Up to 240	9 – 30	LOS, Perinatal characteristics, NAS pharmacologic management, rates of breastfeeding, maternal participation in ODP/VODP, child apprehension
**After discharge** (consenting participants at 6 months)	Up to 240	24	Maternal: participation in ODP/VODP, breastfeeding duration, involvement with Children’s Services, maternal depression (Edinburgh), parenting self-efficacy, quality of life Baby: NAS pharmacologic management, short-term developmental assessment using the Ages and Stages Questionnaire: SE-2 and ASQ 3

De-identified data will be collected and managed using REDCap electronic data capture tools hosted at The University of Alberta [57, 58]. REDCap (Research Electronic Data Capture) is a secure, web-based software platform designed to support data capture for research studies. In addition to chart review, provincial and national health related databases will be used to collect baseline LOS, perinatal characteristics, and data to inform the economic analysis. Data linkage will be through unique identifiers and probabilistic linkage. Data collection will be coordinated by site champions and the NASCENT study investigators. Confidentiality will be maintained throughout the study. Only study investigators will have access to the final dataset.

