### Aim 1: Assess the impact of the rooming-in model of care intervention

#### Aim 1: design

A Stepped Wedge Cluster Randomized Controlled Trial (SW-cRCT) will be conducted with 8 participating sites in Alberta over the course of the study. The SW-cRCT is ideally suited to interventions that require implementation by multiple sites with impact on workflow and the structure of care delivery [55]. This design includes randomized sequential roll out of the intervention to all sites over time. Baseline data acts as the pre-intervention control comparisons and secular trends can be accounted for due to concurrent control groups for most periods. The analysis can also assess whether the impact of the intervention changes over time.

We intend to introduce NASCENT at a new hospital every 3 months following a minimum of 6 months of initial baseline data collection as illustrated in Fig. 2. Hospitals will implement the intervention following a computer-generated stratified random allocation sequence created by the independent study statistician. Stratification based on ‘readiness’ will be used to allow the two sites with existing rooming-in programs and experience to implement early in the study to inform care at sites implementing subsequently.

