**Fig. 2 Fig2:**
[figure not shown]
The NASCENT stepped wedge cluster design. Launch phase: baseline anonymous data collection (continues through all phases). Pre-implementation phase: formative readiness evaluation and development of tailored interventions. Implementation phase: targeted interventions, participant data collection, formative evaluation. Post implementation: formative evaluation and 6-month health and social assessment

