#### Sample size/feasibility

The mean NICU LOS over the last 10 years has consistently been 15 days (reported above) so it was selected as a conservative counterfactual and standard deviation (SD) was set at 3 days based on local and national data to provide adequate power to detect small differences in LOS. Intra-cluster correlation (ICC) was conservatively estimated at 0.1. With 8 sites, 8 initiation steps, and 1 site initiated per step (Fig. 2) over the course of 3 years, a mean LOS of 15 days (SD 3 days), and an ICC of 0.1, the study will have at least 80% power with a two-sided 5% significance level to detect a 19% difference (2.75 days) in NICU LOS.

There were 4.35 cases per 1,000 live births in 2018/2019 and approximately 56,000 livebirths in Alberta in 2018, thus an estimated 244 affected newborns are born per year. Given the rate of rise of NAS cases over the last decade it is likely that approximately 300 infants will be diagnosed with NAS yearly by 2023. Given that 75% of infants with NAS are currently admitted to NICU in Alberta, this corresponds to 225 patients being admitted to NICU by 2023.

Approximately 169 patients/year will be eligible for inclusion in the study (75% of the estimated 225 patients/year) [42]. We estimate that 4 to 6 mother-infant dyads would participate at each implementation site in each 3-month study period. Based on the 70% maternal participation rate of the MMUNA program it is estimated that approximately 20–30 mother-infant dyads would participate in a rooming-in model of care in Year 1, 90 in Year 2, and an increase to 120 dyads/year by the end of year 3, for a total of 240 expected participating dyads during the NASCENT study. 75% of participating dyads in the rooming-in model of care are expected to take part in the research (*i.e*., secondary health outcomes and 6 months follow up) considering the population involved.

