### Mother-Infant dyad outcomes analysis

#### Statistical Analysis

NICU LOS was chosen as the primary outcome because NICU admission may occur for several medical reasons unrelated to NAS and a difference in LOS may be more meaningful in understanding NAS severity. Cases with no NICU admission will be assigned a NICU LOS of 0 days. Generalized Linear Mixed Models and Estimating Equations will be used in analyzing the primary and secondary outcomes: rates of pharmacological management of NAS, child apprehension, maternal participation in an ODP, maternal mental health, parenting self-efficacy, quality of life at discharge at 6 months follow up and, babies’ developmental outcomes at 6 months follow-up (see aim 1 above).

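### The protocol contradicts itself on whether drug treatment, breastfeeding and child apprehension are collected for non-consenting infants after roll-out; on one reading, two secondary comparisons would carry selection bias

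*Protocol article*

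**What the plan says.** Some places in the protocol article point towards restricted collection after roll-out:

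- Data collection and management, text: "Anonymous LOS data will be collected from administrative data for NAS admissions at all sites pre-initiation and at each implementation phase", and this is "for patients that are not consenting participants in the study". Only LOS is named. Standardized forms at discharge and at 6 months are for consenting participants.
- Sample size/feasibility: "75% of participating dyads in the rooming-in model of care are expected to take part in the research", and a parenthesis there explains the research as secondary health outcomes plus the 6-month follow-up.
- Target population: evaluation is aimed at dyads admitted to rooming-in.
- Table 1, anonymous row, months column: 6–27, with 160–240 dyads.

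Others point towards full collection:

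- Table 1, same row, label: "Anonymous) Throughout all phases". Its variables are "LOS in NICU, pharmacological management, breastfeeding at discharge and apprehension rates".
- Figure 2 caption, launch phase: "baseline anonymous data collection (continues through all phases".

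The Statistical Analysis section lists among the secondary outcomes "rates of pharmacological management of NAS, child apprehension, maternal participation in an ODP". It does not say which infants enter those analyses after roll-out.

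**The concern.** Drug treatment and child apprehension are analysed secondary outcomes, and the abstract names a fall in each as an expected result. Table 1 plans both in the control months (anonymous row) and after roll-out (consenting row). If non-consenters drop out of the data at crossover, the control side is an unselected series and the intervention side is the subset whose mothers roomed in and agreed to research.

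The mixed model cannot repair this. Site effects are constant over time and period effects are common to all sites. The selection switches on at each site on the day that site crosses over, so it coincides with the treatment indicator and is estimated as part of the effect. Outcomes that were never extracted may not be recoverable later.

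**Working it through.** **1. The plan's own recruitment figures.** 56,000 × 4.35/1,000 = 243.6 (stated 244). 300 × 0.75 = 225. 225 × 0.75 = 168.75 (stated 169 eligible a year). 0.70 × 168.75 = 118 a year (stated 120 by the end of year 3). 20–30 + 90 + 120 = 230–240 (stated 240). All reproduce.

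**2. What months 6–27 mean.** Aim 1: design states: "We intend to introduce NASCENT at a new hospital every 3 months following a minimum of 6 months of initial baseline data collection". With eight sites over 36 months:

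- control months per site: 6, 9, 12, 15, 18, 21, 24, 27 (sum 132)
- post-roll-out months per site: 30, 27, 24, 21, 18, 15, 12, 9 (sum 156)

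Table 1's 6–27 (anonymous row) and 9–30 (consenting row) are exactly these two spans. The months cell of the anonymous row therefore describes control time only and contradicts the row's label.

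**3. Expected infants.** Assume 169 a year for three years, all at the eight sites and spread evenly over 288 site-months:

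- total: 169 × 3 = 507
- control: 507 × 132/288 = 232
- post-roll-out: 507 × 156/288 = 275

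The row's count of 160–240 sits near the control-only figure. With non-consenting post-roll-out infants added, it would be about 363 (232 + 130) or 327 (232 + 95), using the numbers missed in step 4. The count also fits the months better than the label.

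**4. Share observed after crossover if the text and months govern.**

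| Basis | Observed | Share of 275 | Missed |
|---|---|---|---|
| 70% room in × 75% consent | 144 | 52.5% | 130 |
| 75% of the stated 240 dyads | 180 | 65% | 95 |

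The two rows differ because 0.70 × 275 = 192 rooming-in dyads, not 240. The plan does not reconcile them, so I carry both.

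**5. Illustration of the bias with no true effect.** Let *c* be the share observed, *r* the risk in unobserved relative to observed infants (assumed), and *P* the overall risk. The observed risk is *P* / [*c* + (1 − *c*)*r*].

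For apprehension take *P* = 34%, a proxy: in the pilot, 66% of babies went home with their mothers before the programme.

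- *c* = 0.525: *r* = 1.5 gives 0.34/1.2375 = 27.5%; *r* = 2 gives 0.34/1.475 = 23.1%; *r* = 3 gives 0.34/1.95 = 17.4%. Spurious fall: 6.5, 10.9 and 16.6 points.
- *c* = 180/275 = 0.6545: *r* = 1.5 gives 0.34/1.1728 = 29.0%; *r* = 3 gives 0.34/1.691 = 20.1%. Spurious fall: about 5 and 14 points.

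For drug treatment take *P* = 67%, the pilot's pre-programme morphine rate, with *c* = 0.525: *r* = 1.25, 1.5 and 2 give 60%, 54% and 45%, a spurious fall of 7, 13 and 22 points.

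If the Table 1 label governs, *c* = 1 and the bias is zero.

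**The case against.** A reader might infer that the trial will definitely compare all control infants with about half of those born after roll-out. The documents do not support that as settled. The LOS-only sentence covers the time before initiation and every later phase alike, so by itself it creates no asymmetry. Read strictly, it would leave these outcomes without anonymous data in the control months too. If Table 1 shows it to be shorthand before crossover, it may be shorthand afterwards. The row label and the Figure 2 caption both say that anonymous collection continues. This objection stands, and it makes the finding a contradiction with a conditional consequence. The caption names no variables, however, so it is also compatible with LOS-only collection, and the label is contradicted by its own row.

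A reader might also infer that mothers whose infants need drug treatment would decline consent for that reason. The protocol aims to recruit before the delivery admission and allows consent before or immediately after delivery, while the Background says NAS commonly appears at 24–48 hours. Need for treatment would therefore usually come too late to drive consent. Selection through maternal circumstances remains possible, but nothing in the documents gives its size.

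It can be said that the analysis population belongs to the analysis plan, which is not shown. That is fair for the analysis set. It does not cover which items may be extracted without consent, because an analysis plan cannot restore data that were not collected.

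Finally, the counts are soft. The 169 is built on a province-wide projection for 2023, and the 34% and 67% come from one pilot programme. This too stands.

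**Conclusion.** The contradiction is real: the LOS-only sentence against Table 1's variable list, and within Table 1 the label against the months and count. If the text and months govern, 52.5% of eligible infants, or up to about 65%, would supply drug treatment and apprehension data after crossover, against all infants in control. The direction and size of any bias are unknown. The falls of about 6.5–17 points at 52.5% capture are illustrations that rest on an assumed risk ratio of 1.5–3 and a proxy risk. The 52.5% needs only the plan's two participation rates; the 65% also needs the even spread over sites and months.

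It would be wrong to extend this point to the primary outcome: LOS for non-consenting infants is explicitly collected in every phase. Because only secondary outcomes are touched and one reading of Table 1 already intends full collection, I rate this below a must-fix. It should still be settled before the first site rolls out.

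**What to change.** 1. In Data collection and management, amend the sentence so that LOS, pharmacological management, breastfeeding at discharge and apprehension are extracted anonymously for all eligible infants, at every site and in every period.
2. In Table 1, set the months and dyad count of the anonymous row to agree with its label.
3. State that drug treatment and apprehension are analysed in that all-eligible set, classified by whether the site had crossed over in that period. Keep the consented forms for items that need contact with the mother, such as the 6-month follow-up.

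The cost is an extension of an extraction already planned for the control months, covering about 95–130 more infants, and possibly an ethics amendment. The trial status is not yet recruiting, so no data are lost by changing now. The estimated effects will probably be smaller, because infants whose mothers did not room in would then count.

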Despite the evidence and experience gained, the practice of the rooming-in approach is limited in Alberta. It has been recognized that introducing guidelines and models of care without a detailed and adaptive implementation strategy does not lead to changes in care or improved outcomes; intervention and purposeful implementation are required [45]. Implementation of a rooming-in model requires readiness development of several components, including care teams, education and training, partnerships, and referral and communication pathways [46]. NASCENT is specifically designed to address the gap in adoption of evidence-based NAS care. The rooming-in model of care will be introduced at 8 acute care hospital sites. The intent is to support teams in developing their NAS rooming-in model of care. Informed by the Consolidated Framework for Implementation Research (CFIR) [47], the Capability-Opportunity-Motivation-Behaviour (COM-B) Framework, and the Behaviour Change Wheel [48], targeted interventions will include identifying site barriers, facilitators, and opportunities for growth, as well as capacity building and facilitation of tailored site operationalization. NASCENT will provide funds to facilitate staff education and training; support the development of provincial standardized care components; and help connect sites for mutual support and as a community of practice. A Provincial Clinical Practice Lead, funded by NASCENT, will develop and coordinate educational programming, onsite and virtual training prior to initiation, roll out of site-specific clinical protocols, virtual mentorship for site champions, care teams and individuals following implementation, and feedback to all sites.

NASCENT will support the hiring of site champions at each of the participating sites who will be instrumental to the implementation [49, 50]. Trained by the study team, they will be the point of contact between the NASCENT research team and the site implementation team. The site champions will collect data; facilitate the work of the site implementation team by introducing the rooming-in model of care through staff education, provide training, and mentorship; and coordinate feedback/evaluation sessions and surveys. Additionally, they will work closely with community organizations to identify and recruit participants as well as help facilitate transitions after discharge from the hospital. They will also liaise with other site champions to share challenges and successes.

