#### Target population (mother-infant dyads)

Evaluation of the intervention outcomes will target mother-infant dyads who are admitted to rooming-in programs at one of the eight participating hospitals in Alberta. Eligibility of a mother-infant dyad to participate in the rooming-in model of care implemented by the NASCENT study/ project will be coordinated by each of the sites according to the following criteria:
*Inclusion criteria*: Infants born at greater than 36 weeks’ gestation and a weight of greater than 2000 g born to mothers who report opioid use during pregnancy. Infants at risk for NAS must be well enough to participate in the rooming-in model of care.
*Exclusion criteria:* Infants born at less than 36 weeks and/or birth weight less than 2000 g. Infants with congenital anomalies will be excluded because at most sites these infants would be admitted to NICU.

The goal is for site champions and study team members to recruit participants prior to hospital admission for delivery, but potential participants will also be approached if their delivery presentation is the first recruitment opportunity. During pregnancy, mothers who wish to participate in rooming-in will be identified through colleagues at community organizations. Consent to participate in the study (*i.e.,* consent to extract data using healthcare number and 6-month follow up)may be obtained prior to or immediately after delivery at the hospital.

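### NICU length of stay comes from different sources depending on consent, and consent arises only under the intervention, so measurement and case capture of the primary outcome can differ by condition

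*Protocol article*

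**What the plan says.** The protocol article, under Data collection and management, assigns the LOS source by consent status.

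- Infants outside the consented group: "Anonymous LOS data will be collected from administrative data for NAS admissions at all sites pre-initiation and at each implementation phase for patients", with the series restricted by the words "for patients that are not consenting participants in the study".
- Consenting participants: "Standardized forms will be used to collect data, including LOS, for consenting participants at discharge and at 6 months follow-up".
- Baseline, a further source: "In addition to chart review, provincial and national health related databases will be used to collect baseline LOS, perinatal characteristics".

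Table 1 places the anonymous series across all phases (months 6–27) and the consenting participants during implementation (months 9–30). The anonymous row names the variable as LOS in the NICU. The consenting row names it only as LOS.

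Under Statistical Analysis, "Cases with no NICU admission will be assigned a NICU LOS of 0 days". Under Target population, consent is described as "consent to extract data using healthcare number" plus the six-month follow-up. Under NASCENT, "The site champions will collect data; facilitate the work of the site implementation team". Data collection and management adds that site champions and investigators coordinate data collection, and that records will be linked by unique identifiers and probabilistic linkage.

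**The concern.** The treatment effect contrasts infants before and after a site crosses over. Nobody is a consenting participant before crossover, so form-based LOS can enter only on the intervention side. Any systematic difference between a form entry and an administrative day count then goes into the estimated effect. Examples are the handling of part days, transfers and observation stays.

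Two features of the text add to this.

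- **The variable.** Rooming-in moves infants to postpartum or pediatric units, so total stay and NICU stay separate most under the intervention. That is where Table 1 drops the NICU qualifier.
- **Case capture.** The administrative series is of NAS admissions: "Anonymous LOS data will be collected from administrative data for NAS admissions". Consenting participants are infants of mothers who report opioid use, whether or not NAS is later recorded. An exposed infant with no NAS record and no NICU stay could enter as 0 days through a form after crossover, while a similar infant before crossover might not be in the administrative series at all. If that happened, it would lower the intervention mean for a reason unrelated to care.

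The size of the LOS difference also feeds the cost-avoidance calculation under Economic analysis, so a shift matters there even when it does not change the significance test.

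**Working it through.** **Sources side by side**

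| Infants | LOS source stated | Condition |
|---|---|---|
| Before site initiation | Administrative data; chart review also mentioned for baseline | Control |
| After initiation, not consenting | Administrative data | Intervention |
| After initiation, consenting | Standardized forms | Intervention |

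Forms appear in one row only. No sentence commits the primary analysis to a single source or day-count rule, or to checking forms against records.

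**Size.** The protocol gives no figure for a form-versus-administrative difference, so there is nothing to reproduce. The following is an illustration.

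Inputs:
- Rooming-in participation 70%, and research participation among those dyads 75% (Sample size/feasibility).
- Current NICU admission of infants with NAS 75% (The setting; Sample size/feasibility).
- Design difference 2.75 days (Sample size/feasibility).
- Assumed: a difference of up to 1 day per NICU admission between the two sources.
- Assumed: a lower admission figure of 50%, and an alternative range of 12–25% for rooming-in infants.
- Assumed: the intervention condition counts all eligible infants after initiation.

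Share of intervention infants measured by form: 0.70 × 0.75 = 0.525.

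Shift in the intervention mean = share by form × proportion admitted × days per admission. An infant never admitted is scored 0, so no counting rule applies.

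| Proportion admitted | Shift (days) | Share of 2.75 days |
|---|---|---|
| 75% | 0.525 × 0.75 × 1 = 0.39 | 14% |
| 50% | 0.525 × 0.50 × 1 = 0.26 | 10% |
| 25% | 0.525 × 0.25 × 1 = 0.13 | 5% |
| 12% | 0.525 × 0.12 × 1 = 0.06 | 2% |

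The shift scales with the assumed difference: half a day per admission halves every entry. It is largest if rooming-in does little to reduce NICU admission and smallest if it works as intended. The sign is unknown.

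The case-capture difference is not in this table. The documents do not say how many exposed infants would lack a NAS record, so no figure is put on it.

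**The case against.** The strongest reply is that the contrast is blurred. Baseline LOS also involves chart review, and a standardized form may be no more than an abstraction sheet for the same hospital record. NICU admission and discharge dates are objective. A journal article may leave counting rules and form completion to a data-management plan. Table 1 uses the NICU label only for the anonymous series, and Sample size/feasibility describes research participation in terms of secondary outcomes and follow-up, so the primary analysis may be meant to rest on administrative data. These arguments limit the likely size. They do not remove the stated rule, which excludes consenting participants from the administrative series and puts LOS on their forms.

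Several stronger readings are tempting, but the documents do not support them.

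- **That every intervention infant is measured by form and every control infant by administrative count.** Non-consenting infants after crossover stay in the administrative series, and control LOS may also involve charts.
- **That unblinded site champions complete the forms.** They collect and coordinate data, but the article does not say who fills in the forms or that their involvement differs by condition.
- **That infants will be counted twice.** Excluding consenters from the anonymous series guards against that, and linkage is planned.
- **That no analysis could correct the difference.** With consented linkage, form and administrative values could be compared in the same infants. Without it, a source indicator would be confounded with consent.
- **That counting rules alone could produce 18–27% of the target** (0.50–0.75 day out of 2.75). That needs every intervention infant measured by form at 50–75% admission.
- **That the control series contains no zero-day infants.** The article does not define NAS admissions as NICU admissions, and it does assign 0 days to infants never admitted.

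**Conclusion.** The point holds as a differential-measurement risk written into the data-collection rule. The intervention condition is mixed-source and the control condition has no form data. The variable label and the way infants are identified also differ between the two streams.

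The counting shift is about 0.26–0.39 day (10–14% of 2.75 days) if forms and records differ by up to 1 day per admission, 52.5% of intervention infants are measured by form and 50–75% are admitted. It is about 0.06–0.13 day (2–5%) if 12–25% are admitted. The 1-day difference and every admission figure except the current 75% are assumptions, and the direction is unknown.

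If the true effect is near the pilot's fall from 10.33 to 0.82 days (9.51 days), a shift of this size would not change the conclusion. Case capture would then be the more important part, because most intervention infants would be scored 0 and what matters is whether comparable control infants are in the dataset. The change is worth making before data collection starts, because the design target is 2.75 days and the correction is inexpensive.

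**What to change.** For the primary analysis, take NICU admission and NICU LOS for every infant in both conditions from the same administrative record. State one case definition for who enters the dataset and one day-count rule, including part days and transfers, and apply both before and after crossover. For consenting participants, obtain the record through the healthcare number that their consent already covers. Name the variable as NICU LOS in both rows of Table 1. Keep the forms for outcomes that administrative data do not hold, and use their LOS entry only for a concordance check. If a single source is already intended, one sentence saying so is enough for the measurement part; the common case definition still has to be stated.

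The cost is a change to the data-management text, waiting for the administrative extract, and a little more linkage work. The administrative collection already runs through all phases, so no new data stream is needed.
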